### Sample size

The sample size for this study is based on the meta-analysis of self-help treatments for anxiety disorders by Haug *et al*.
[13]. An effect size of d =0.83 was derived for PD after comparing the self-help group with the waitlist/placebo group. Because hybrid online training was not integrated into the meta-analysis, we chose a conservative estimation of d =0.60. To examine the efficacy of GET.ON PANIC with a two-tailed t-test (α =0.05; 1-β =0.80), a sample of 45 participants will be needed for each group. Thus, the total sample size for this study will be 90 participants.

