### Primary outcome measure

#### Panic severity

The primary outcome will be the severity of panic and agoraphobia symptoms as assessed by the total PAS score
[34, 35, 48]. This questionnaire was originally developed as a self- and observer-rating scale. In this study, we will use the self-rating questionnaire that was adapted into an online version. The PAS consists of 13 items grouped into five subscales, and an extra item regarding unexpected versus expected panic attacks. The five subscales assess the following areas: panic attacks, agoraphobic avoidance, anticipatory anxiety, daily life limitations, and health concerns (for example, the fear of physical harm or the fear of an organic cause). These subscales can be evaluated separately or as a total score that combines all subscales, ranging from 0 to 52 points. A higher score on the PAS indicates more panic symptoms. The psychometric properties of the scale are satisfactory, with a Cronbach’s alpha of 0.86
[49]. A score of between 0 and 8 indicates no clinically relevant symptoms, scores of between 9 and 28 indicate moderate symptoms, and a score of 29 or higher indicates a severe level of symptoms
[49].

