#### Treatment efficacy

Group differences in the baseline values of the primary outcome will be compared using t-tests to assess whether randomization was successful. Missing data will be addressed following the recommendations of Little and Rubin
[69] and Schafer
[70]. We will analyze the PAS data at eight weeks post-treatment using between-group analyses of covariance with regard to the individual baseline PAS scores, adjusted for sex, age, and socioeconomic status. We will use Cohen’s d to measure the between-group effect size. Cohen’s d will be calculated as the difference between the mean post-test scores of the intervention group and the control group divided by the pooled standard deviation
[71]. All other secondary outcomes will be analyzed in a similar manner.

We will also conduct clinical significance change analyses as described by Jacobson and Truax
[72]. In the first step, we will test whether the changes from pre-test to post-test are statistically reliable and build a reliable change index (RCI). In the second step, we will calculate clinical significance. Based on the RCI, the participants who display a reliable positive change, no change, or a reliable deteriorated change will be classified as responders, non-responders, or deteriorated, respectively
[72]. We will use mixed-model regressions to examine the long-term effect on the primary outcome after three and six months.

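### The only between-group effect size defined is Cohen's d from unadjusted post-test means, while the primary test is a baseline-adjusted ANCOVA; a d built on the adjusted difference would be more precise and would match the test

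*Protocol article*

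**What the plan says.** All of this is in the protocol article.

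- **Primary outcome** (Panic severity): "The primary outcome will be the severity of panic and agoraphobia symptoms as assessed by the total PAS score".
- **Primary test** (Treatment efficacy): PAS at eight weeks is compared by "between-group analyses of covariance with regard to the individual baseline PAS scores, adjusted for sex, age, and socioeconomic status".
- **Effect size** (same paragraph): Cohen's d is used "to measure the between-group effect size" and is "calculated as the difference between the mean post-test scores of the intervention group and the control group divided by the pooled standard deviation". No other between-group effect measure is named for this comparison.
- **Secondary outcomes** (same paragraph): these are to be handled along the same lines.
- **Planning** (Sample size): from a meta-analytic d of 0.83, "we chose a conservative estimation of d =0.60". For a "two-tailed t-test (α =0.05; 1-β =0.80"), "a sample of 45 participants will be needed for each group".

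**The concern.** The p-value and the effect size come from two different estimators. The ANCOVA removes the part of the 8-week difference that is predicted by a chance baseline difference in PAS. The stated d leaves it in, in proportion to the correlation between baseline and 8-week scores. In a trial of 90 people that part need not be negligible.

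Two things are at stake. The first is precision: the trial collects baseline PAS and uses it in the test, but gives up its benefit in the effect size. The second is coherence: the effect shown beside the test can be somewhat larger or smaller than the effect that was tested. The Sample size section frames the expected benefit as a d (0.83, reduced to 0.60), so readers are likely to set the trial's d against those figures.

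Because the article writes the formula out, this is a stated rule and not a detail left to an analysis plan.

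**Working it through.** **Inputs from the article.** Two-sided α = 0.05, power 80%, d = 0.60 and 45 per arm (Sample size); the ANCOVA and the formula for d (Treatment efficacy).

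**Input not in the article.** The correlation r between baseline and 8-week PAS. I assume r = 0.3, 0.5 and 0.7.

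**Step 1: reproduce the planned size.** The normal approximation gives n = 2(1.96 + 0.842)²/0.60² = 43.6, so 44 per arm. The exact t calculation gives 44.59, so 45 per arm, with 80.4% power at 45. The stated figure reproduces.

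**Step 2: precision.** On the SD = 1 scale, with the SD treated as known and baseline PAS as the only covariate:

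- Unadjusted: SE = √(2/45) = 0.211.
- Adjusted: SE = √(2(1 − r²)/45).

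| r | SE unadjusted | SE adjusted | Variance ratio 1/(1 − r²) |
|---|---|---|---|
| 0.3 | 0.211 | 0.201 | 1.10 |
| 0.5 | 0.211 | 0.183 | 1.33 |
| 0.7 | 0.211 | 0.151 | 1.96 |

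**Step 3: shift from chance baseline imbalance.** The baseline difference also has SE √(2/45) = 0.211 SD, so its 95% range is ±1.96 × 0.211 = ±0.41 SD. It moves the unadjusted d by r times the imbalance.

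- Typical absolute shift, r × 0.211 × √(2/π): 0.05, 0.08 and 0.12 at r = 0.3, 0.5 and 0.7.
- 95% limit at r = 0.5: 0.5 × 0.413 = 0.21.
- For one observed imbalance of 0.3 SD: 0.09, 0.15 and 0.21.

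These figures ignore the stratified randomisation.

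**Step 4: simulation check.** I used 20,000 trials per scenario, 45 per arm, true d = 0.60, with d computed from the estimated pooled SD in each trial. The standard deviation of the unadjusted d was 0.218 to 0.219. That of the adjusted d was 0.210, 0.192 and 0.160 at r = 0.3, 0.5 and 0.7. The mean absolute gap between the two was 0.05, 0.08 and 0.12, which agrees with step 3. The ANCOVA and an unadjusted t-test on the same data disagreed about significance in 7%, 12% and 18% of trials. In most of these (5%, 11% and 17% of all trials) only the ANCOVA was significant. The two estimates had opposite signs in about 0.2% to 0.3% of trials.

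**The case against.** **The two quantities do different jobs and neither is wrong.** The ANCOVA tests and d describes. Under randomisation both aim at the same mean difference. A reader might infer that the stated d is biased, or that the primary p-value is compromised. The article supports neither reading: the imbalance is ordinary sampling error that the standard error of an unadjusted d already contains, and the primary test and its type I error are untouched. This stands, and it limits the point to precision and coherence.

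**The article does not say the adjusted difference will go unreported.** A condensed article may leave that to an analysis plan. This also stands, so its absence is not the complaint. What remains is that the one effect size the article does define is written out without adjustment.

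**A post-test d matches the planning quantity.** The sample size rests on an unadjusted t-test, so the choice is coherent. But an adjusted difference over the same pooled SD is on the same scale, so nothing is lost by adding it. How other internet trials computed d cannot be seen here, so no claim about comparability can be made in either direction.

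**The size is easy to overstate.** The 0.21 shift, about a third of 0.60, is a 95% limit at one assumed r. The typical shift there is 0.08, about 14% of 0.60. At r = 0.3 the standard error falls by less than 5%. Randomisation is stratified by clinical or subclinical symptomatology and by agoraphobia, which probably narrows baseline imbalance. If the strata explained 30% of baseline PAS variance (an assumption) and balanced well, ±0.41 would become 0.413 × √0.7 = ±0.35. The PAS 9 to 28 entry range may also lower r. All of this stands.

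**No test on d is planned.** The disagreement rates in step 4 therefore compare the ANCOVA with a test the protocol does not contain. They show how far the two estimates can diverge; they are not rates of conflicting planned results.

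**Conclusion.** The point holds as a modest one about reporting. The stated d is unbiased but less precise than a d built on the ANCOVA the trial already plans, and it carries chance baseline imbalance that the ANCOVA removes. The direction holds for any r other than zero. The size depends on r, which the article does not give: the variance of the unadjusted estimate is about 1.10, 1.33 or 1.96 times that of the adjusted one at r = 0.3, 0.5 or 0.7, and the typical gap in d is about 0.05, 0.08 or 0.12. These figures assume 45 analysed per arm, baseline PAS as the only covariate and no gain from stratification. Sex, age and socioeconomic status are not in the calculation.

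The primary test, its error rate and the sample size need no change.

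**What to change.** In Treatment efficacy:

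1. Name the ANCOVA-adjusted mean difference in 8-week PAS, with its 95% CI, as the primary estimate.
2. Define the main Cohen's d as that adjusted difference divided by the pooled, unadjusted SD already planned, using the same intention-to-treat data and missing-data method as the ANCOVA. Dividing by the residual SD of the model would change the scale and should be avoided.
3. State how the CI for d is obtained: either the SD is treated as fixed, or the whole calculation is bootstrapped. The ANCOVA alone gives a CI for the difference, not for d.
4. Keep the post-test d, labelled as unadjusted and descriptive, for comparison with other trials.
5. Apply the same rule to the secondary outcomes measured at baseline.

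The cost is a few sentences of wording, with no new data and no change to the 90 participants. The small downside is that two effect sizes appear for each outcome, so the labels must show which is the main one.

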#### Economic analyses

We will conduct an economic evaluation by performing a cost-effectiveness analysis (CEA) and a cost-utility analysis (CUA) from a societal perspective. The clinical outcome of the CEA will be the severity of panic symptoms as assessed by the PAS. Quality-adjusted life years (QALYs) will be calculated for the CUA. A non-parametric bootstrapping method with 95% confidence intervals will be used to assess the differences between the intervention and control groups. The intervention and waitlist control groups will be compared in terms of incremental costs and incremental effects. Thus, we will calculate the incremental cost-effectiveness ratio (ICER). Bootstrapping via 5,000 iterations will be used to quantify the uncertainty in the ratios and to test the robustness of the ICER. The results will be displayed on a cost-effectiveness plane and via a cost-effective acceptability curve. A multi-way sensitivity analysis will be conducted to test the robustness of the base-case findings. For instance, these analyses will integrate data based on the EMA to reduce the retrospective bias of self-reported panic symptom severity.

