### Procedure

Participants will be recruited from the general population via an online health center website postings in anxiety- and panic-related online forums, and newspaper articles about the research project. Participants will receive an email with detailed information about the study. Afterwards, participants will be invited to complete a screening questionnaire to evaluate their study eligibility. Participants will then have access to the online training platform via their email address (as their username) and a self-selected password. If participants meet the eligibility criteria, they will receive an ID number. Participants can then opt into study participation by reading, signing, and returning the informed consent document. Participants will then receive a link to complete the baseline questionnaires. After completing the baseline questionnaires (t0), participants will be invited to take part in a telephone interview. This interview has two purposes. The first is for a trained interviewer to conduct a diagnostic interview (SCID-I) to provide a detailed sample description
[41, 42]. The second is to conduct an observer rating of anxiety symptoms using the Hamilton Anxiety Scale (HAM-A)
[43] to strengthen the robustness of the self-report measures. Assessors blind to the participant treatment condition will conduct all observer-based ratings. The post-treatment measurement (t1) will be assessed eight weeks after randomization. Follow-up measures will be conducted at three months (t2) and six months (t3) after randomization. All questionnaires at the baseline, post- and follow-up assessments are self-reported and conducted via the internet, with the exception of the observer rating HAM-A, which will be performed at t0 and t1 via telephone. The waitlist control group will receive the treatment after t3.

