**Table 2 Tab2:** **Overview of instruments per time of assessment**

Assessments	Screening	T0	T1	T2	T3
Sociodemographic data	**x**	**-**	**-**	**-**	**-**
Suicidality (Item 9, BDI-II)	**x**	**-**	**-**	**-**	**-**
Diagnosis (SCID-I, sections for anxiety disorders and current depressive episode)	**-**	**x**	**-**	**-**	
Panic and agoraphobia severity, self-rating (PAS)	**x**	**x**	**x**	**x**	**x**
Panic and agoraphobia severity, observer-rating (HAM-A)	**-**	**x**	**x**	**-**	**-**
Agoraphobic cognitions (ACQ)	**-**	**x**	**x**	**x**	**x**
Body sensations (BSQ)	**-**	**x**	**x**	**x**	**x**
Agoraphobic avoidance (MI)	**-**	**x**	**x**	**x**	**x**
Depressive symptoms (CES-D)	**-**	**x**	**x**	**x**	**x**
Quality of life (EQ-5D, SF-12)	**-**	**x**	**x**	**x**	**x**
Economic evaluations (TiC-P)	**-**	**x**	**-**	**-**	**x**
Negative effects of online health trainings	**-**	**-**	**(x)**	**(x)**	**(x)**
Attitudes towards seeking psychological help	**-**	**-**	**(x)**	**-**	**-**
User satisfactory	**-**	**-**	**(x)**	**-**	**-**
Technology acceptance of smartphone app	**-**	**-**	**(x)**	**-**	**-**
Usability of smartphone app (SUS)	**-**	**-**	**(x)**	**-**	**-**

T0 = Baseline, T1 = 8 weeks, T2 = 3 months, T4 = 6 months.

Assessments: x = intervention and control group, (x) = intervention group only.

ACQ, Agoraphobic cognitions questionnaire; BDI-II, Beck Depression Inventory II; BSQ, Body sensations questionnaire; CES-D, Center for epidemiological studies depression scale; EQ-5D, EuroQol; HAM-A, Hamilton anxiety scale; MI, Mobility inventory; PAS, Panic and agoraphobia scale; SCID-I, Structured clinical interview for DSM-IV Axis I Disorders; SF-12, Short form 12; SUS, System Usability Scale; TiC-P, Trimbos and the Institute of Medical Technology Assessment Cost Questionnaire for Psychiatry.

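### The economic analysis specifies no baseline adjustment for incremental QALYs and costs, although EQ-5D and TiC-P are collected at T0; adjusting would add precision at no cost

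*Protocol article*

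**What the plan says.** The economic analyses section of the protocol article gives the CEA and CUA their own method: "A non-parametric bootstrapping method with 95% confidence intervals will be used to assess the differences between the intervention and control groups". It continues: "The intervention and waitlist control groups will be compared in terms of incremental costs and incremental effects". An ICER follows, with 5,000 bootstrap iterations, a cost-effectiveness plane, an acceptability curve and a multi-way sensitivity analysis. The CEA effect is PAS severity. For the CUA, "Quality-adjusted life years (QALYs) will be calculated for the CUA", with no statement of how. The section names no regression model and no covariate.

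In Table 2 the row "Quality of life (EQ-5D, SF-12" is marked for both arms at T0, T1, T2 and T3. The row "Economic evaluations (TiC-P" is marked for both arms at T0 and T3 only.

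Under treatment efficacy, the eight-week PAS comparison uses "between-group analyses of covariance with regard to the individual baseline PAS scores, adjusted for sex, age, and socioeconomic status". That paragraph ends: "All other secondary outcomes will be analyzed in a similar manner". Randomization is stratified by clinical or subclinical symptomatology and by agoraphobia, not by utility or cost.

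**The concern.** A six-month QALY is built from utilities over the whole period. If it is the area under the utility curve, it contains the T0 utility itself, and the later utilities are correlated with T0. A chance T0 difference between arms therefore passes into the incremental QALY. Prior cost can act in the same way on incremental cost.

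Cost-effectiveness is a stated aim, but the sample was sized for the PAS comparison alone, so precision for the ICER is scarce. The data that would recover some of it are already being collected. The PAS effect adds a further point: it is baseline-adjusted in the efficacy section, while no adjustment is specified where it becomes the CEA effect. The two sections could then report PAS effects estimated in different ways.

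**Working it through.** **The plan's own figure.** The article states 45 per arm for d = 0.60, two-sided α = 0.05 and power 0.80. The two-sample t-test gives 44.59, rounded up to 45, with power 80.4% at 45. The stated sample size is reproduced. It concerns PAS only; the article gives no figure for EQ-5D variability, QALYs or costs.

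**Inputs from the article.** Assessments at baseline and eight weeks, then "Follow-up measures will be conducted at three months (t2) and six months (t3) after randomization"; 45 per arm.

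**Assumptions, not in the article.** QALYs by the trapezoidal rule; the same utility SD at every visit; the same correlation ρ between every pair of visits, 0.3 to 0.8. Where an SD is needed, 0.20 serves as illustration.

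**Step 1: weights.** With times 0, 8/52, 0.25 and 0.50 years, the trapezoidal weights are:
- T0: (8/52)/2 = 0.077
- T1: 0.25/2 = 0.125
- T2: (0.50 − 8/52)/2 = 0.173
- T3: (0.50 − 0.25)/2 = 0.125

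They sum to 0.5 year. The follow-up weights sum to 0.423, and the squared weights sum to 0.0671.

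**Step 2: variance removed by adjustment.** In units of the utility variance:
- QALY variance: v = ρ × 0.5² + (1 − ρ) × 0.0671
- slope of the QALY on T0 utility: c = 0.077 + 0.423ρ
- share of variance removed by regression on T0: c²/v

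The SD cancels in this share. The SE of the between-arm difference is SD × √(2v/45) unadjusted and SD × √(2(v − c²)/45) adjusted.

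| ρ | v | c | c²/v | SE unadjusted (SD 0.20) | SE adjusted (SD 0.20) |
|---|---|---|---|---|---|
| 0.3 | 0.122 | 0.204 | 34% | 0.0147 | 0.0120 |
| 0.4 | 0.140 | 0.246 | 43% | 0.0158 | 0.0119 |
| 0.5 | 0.159 | 0.288 | 52% | 0.0168 | 0.0116 |
| 0.6 | 0.177 | 0.331 | 62% | 0.0177 | 0.0109 |
| 0.7 | 0.195 | 0.373 | 71% | 0.0186 | 0.0100 |
| 0.8 | 0.213 | 0.415 | 81% | 0.0195 | 0.0085 |

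**Step 3: size of a chance baseline shift.** The SE of the T0 difference is SD × √(2/45), which is 0.042 for SD 0.20. Multiplied by c, its 1.96-SE carry-over into the incremental QALY is 0.017 at ρ = 0.3, 0.024 at ρ = 0.5 and 0.034 at ρ = 0.8. Over SD 0.15 to 0.25 and ρ 0.3 to 0.7 the range is 0.013 to 0.039.

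**Step 4: comparison with an assumed gain.** A utility gain of 0.05 held from T1 to T3 is worth 0.05 × 0.423 = 0.021 QALY. With SD 0.20 and ρ = 0.5, the chance that the carry-over is at least that large in either direction is about 8%. Over SD 0.15 to 0.25 and ρ 0.3 to 0.7, the chance is 5% to 52% for a gain of 0.03, 0.1% to 28% for 0.05, and about 0% to 9% for 0.08.

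**Costs.** The article gives neither a cost SD nor a correlation between T0 and T3 costs, so no calculation is possible.

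**The case against.** The strongest reply is that the economic section is silent on adjustment and does not rule it out. Bootstrapping is a way of obtaining intervals and works equally well on a regression coefficient. The article is condensed, and a separate analysis plan may name the covariates. Quality of life and economic evaluation are also listed under secondary outcome measures, so the sentence extending the ANCOVA to other secondary outcomes might be meant to cover them.

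Much of this stands. A reader might infer that the plan commits to an unadjusted comparison, or that the T0 TiC-P will go unused; the article says neither. The extension sentence does not settle the matter, however. It sits under treatment efficacy, after an eight-week ANCOVA, whereas QALYs and costs accumulate over time and have a section and method of their own. A QALY also has no baseline value of its own, so the covariate has to be named.

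A reader might also infer that imbalance biases the ICER, or that it will typically be as large as the QALY gain. Neither is supported. Randomization keeps the plain difference unbiased on average, and the carry-over is already part of the unadjusted SE that a participant-level bootstrap reflects. The comparison with the gain rests on an SD, a correlation and a gain that the article does not give. Over most of the assumed ranges an imbalance of that size is possible, not typical.

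**Conclusion.** The point holds as an improvement to the method; it does not show an error. Followed as written, the economic section yields a valid but less precise QALY comparison than the collected data allow, and a single-trial ICER that is more exposed to chance baseline imbalance. Under trapezoidal QALYs and equal correlation of 0.3 to 0.8 between visits, adjustment for T0 utility removes about 34% to 81% of the variance of the incremental QALY. This share does not depend on the assumed SD, but it does depend on the correlation, which the article does not give. For costs the argument is qualitative only.

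**What to change.** State in the economic analyses section that, within each of the 5,000 bootstrap resamples:
- incremental QALYs are estimated by regression on arm and T0 EQ-5D utility;
- incremental costs are estimated by regression on arm and T0 TiC-P cost;
- the PAS effect in the CEA is estimated by regression on arm and T0 PAS.

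Each regression also includes the two stratification factors. Resample participants, so that a participant's costs and effects stay together, and report the unadjusted result as a sensitivity analysis. If an analysis plan already says this, a cross-reference is enough. The cost is a few sentences and a few lines of code; every variable is already scheduled for collection.

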One potentially promising method to enhance the adherence to, and efficacy of, internet-based interventions for PD might be to complement interventions with components that are delivered through clients’ smartphones. Mobile components might assist patients in overcoming several limitations of traditional desktop- and laptop-based interventions. For example, these barriers might include situations in which the clients start to engage in exposure exercises in their natural environment (as is typical for *in vivo* exposure exercises) and are subsequently required to leave their desktop PCs or laptop. This results in a dilemma - either exposure exercises are exclusively conducted at the client’s desk or they are conducted without the device and therefore lack support during the exposure exercises. Consequently, clients are more likely to disengage from the intervention. In contrast, clients often carry their smartphones with them in almost any situation, and they might support clients in successfully completing the intended exposure exercise
[19–21]. Moreover, when desktop PCs or laptops are used to monitor symptoms of PD to identify factors that cue panic attacks and avoidance, clients typically use daily or weekly electronic diary entries, which are likely biased by memory effects because clients must complete these diaries retrospectively and not in real-time
[22–28]. In contrast, a mobile-based PD intervention tool can be used to assess the symptoms of PD in real-time through ecological momentary assessment (EMA) approaches
[29–33]. Finally, a PC-based program can only prompt appropriate coping responses when the PC is on and clients are near it. Therefore, it is not available in other situations of their daily lives in which they inevitably encounter stimuli that trigger the symptoms of PD. In contrast, a mobile device that is nearly always on, or near, the client can be used as an ecological mobile intervention (EMI) device and prompt coping responses, potentially those that have been specifically identified as effective for the individual based on the EMA function of the device. Despite these advantages, no data are currently available regarding the efficacy of online-based interventions for PD that integrate a mobile component.

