## Methods/Design

### Study design

We will conduct an RCT with two arms: an internet-based self-help intervention supported by a mobile application with minimal guidance from a coach (GET.ON PANIC), and a waitlist control group who will receive the intervention after a six-month follow-up assessment. Assessments will be conducted prior to randomization, at post-treatment (eight weeks), as well as at the three- and six-month follow-up assessments (see Figure 
1). The Ethical Committee of Marburg approved this study (number: 2013-23 K), and it was registered with the German Clinical Trial Register (registration number: DRKS00005223).

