### Intervention

GET.ON PANIC is a hybrid internet-based self-help intervention with minimal therapeutic guidance based on CBT principles
[18, 44–46]. The hybrid online training consists of two components: a browser-based section (desktop PC or laptop) and a mobile application (smartphone app). The intervention is divided into six modules: psychoeducation, interoceptive exposure, *in vivo* exposure, two modules of cognitive restructuring, and relapse prevention (see Table 
1). Using responsive web design, participants can use the program on a desktop PC, a laptop, a tablet, or a smartphone. An integrated read-aloud function allows participants to follow the lessons via audio narration. The app addresses interoceptive and *in vivo* exercises as well as diary and relaxation exercises. Detailed information about the development of the app can be found in the paper by [name] *et al*.
[47].In the first module, participants will receive an overview of the different modules and the practical procedure of the online training. Information about PD will be provided, and personal goals will be defined. In addition, a mobile diary will be introduced to the participants. The emphasis of the second module is interoceptive exposure. The theoretical background of the relationship between bodily symptoms and anxiety will be provided in an interactive way with videos and writing exercises. The app contains three interoceptive exposure packages, each consisting of four different tasks. In module three, participants will rank their individual anxiety provoking situations in a hierarchy before beginning the app-assisted *in vivo* exposures (see Figure 
2). In addition, participants will continue with the second of the interceptive exposure exercises, which address dizziness.

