#### Diary data

EMA data will be collected via the mobile application GET.ON PANIC APP
[47]. This app contains a diary where clients can record their panic attacks and monitor their progress using daily summaries. With regard to the latter, clients will summarize their general anxiety levels, their degree of avoidance, and their moods each evening. The application also records the type and number of exposure exercises performed by the client.

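### The economic sensitivity analysis relies on app diary (EMA) data that only the intervention arm can supply, so it cannot correct the between-arm incremental effect for recall bias

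*Protocol article*

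**What the plan says.** The Economic analyses section sets up a between-arm comparison: "The intervention and waitlist control groups will be compared in terms of incremental costs and incremental effects". Its effect measure is fixed: "The clinical outcome of the CEA will be the severity of panic symptoms as assessed by the PAS". A multi-way sensitivity analysis is to test the base case. As an example of its content, the section says "these analyses will integrate data based on the EMA to reduce the retrospective bias of self-reported panic symptom severity".

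The Diary data section names the source: "EMA data will be collected via the mobile application GET.ON PANIC APP". It describes the content as records of panic attacks plus evening ratings of general anxiety, avoidance and mood. The Intervention section makes the smartphone app one of the two components of the training, next to the browser-based part.

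Study design defines the comparator as "a waitlist control group who will receive the intervention after a six-month follow-up assessment", and Procedure repeats this: "The waitlist control group will receive the treatment after t3". The Discussion also places the controls' training after the last assessment.

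Table 2 marks the Panic and Agoraphobia Scale (PAS) for both arms at T0 to T3. It has no row for the diary or EMA in either arm. Table 1 lists the daily diary in training weeks 1 to 5.

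**The concern.** A sensitivity analysis of a between-arm difference needs an input that exists in both arms. Here the added input can come from one arm only, and the stated purpose is to correct the severity measure on which the contrast rests.

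Recall error in the self-rated PAS is present in both arms. To the extent that it is similar, it cancels in the difference. Correcting it in one arm removes that cancellation and can create a bias where there was little. An analysis meant to show that the base case is robust could then move away from it for reasons unrelated to treatment, and a reader could not tell a method difference from a treatment effect.

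**Working it through.** **Step 1. Who can supply EMA data, and when.**
- Source: the app (Diary data). No other source is named.
- Who has the app: recipients of the training (Intervention).
- When controls receive the training: after t3, at six months (Study design, Procedure, Discussion).
- Last time point of the comparison: t3.

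No control can therefore contribute EMA data inside the comparison window. This is inferred from several sections rather than stated in one sentence, but nothing in the article contradicts it.

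**Step 2. Whether the diary could stand in for the PAS within the intervention arm.**
- Content: the diary covers attacks, anxiety, avoidance and mood. The PAS total (0 to 52) has five subscales, which include daily life limitations and health concerns. A mapping between the two would be needed, and none is described.
- Timing: Table 1 lists the diary in weeks 1 to 5. T1 is at eight weeks, T2 at three months and T3 at six months. No EMA collection is listed at any of these.
- Baseline: the diary is introduced in the first training module, so there is no EMA value from before randomization.
- Costs: Table 2 collects the cost questionnaire at T0 and T3 only, so the diary weeks do not match the cost horizon either.

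**Step 3. What a one-arm correction does.** Let S be true severity, r the error of the PAS, and e the error of an EMA-based severity measure. A higher score is worse, so the effect is control minus intervention.
- PAS in both arms: (S_C + r_C) − (S_I + r_I) = Δ + (r_C − r_I). If the two errors are equal, the result is Δ.
- PAS in controls, EMA-adjusted severity in the intervention arm: (S_C + r_C) − (S_I + e) = Δ + (r_C − e).

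The method difference r_C − e enters in full. Its sign is unknown.

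**Step 4. Illustrative size.** The only effect size given for the design is d = 0.60 (Sample size). That section's own figure reproduces. The normal approximation gives n = 2(1.960 + 0.842)²/0.60² = 43.6, so 44 per arm. The exact two-sample t-test gives 44.59, so 45 per arm, with power 0.804. The point does not depend on this; it only supplies a reference effect.

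Assumption, not from the documents: a one-arm method shift b of 0.1 to 0.3 SD. Apparent effect = 0.60 ± b. ICER = ΔC/ΔE, so at fixed incremental cost ΔC the ICER is multiplied by 0.60/(0.60 ± b).

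| b (SD) | d if the shift favours the intervention | ICER factor | d if the shift goes against it | ICER factor |
|---|---|---|---|---|
| 0.1 | 0.70 | 0.60/0.70 = 0.86 | 0.50 | 0.60/0.50 = 1.20 |
| 0.2 | 0.80 | 0.60/0.80 = 0.75 | 0.40 | 0.60/0.40 = 1.50 |
| 0.3 | 0.90 | 0.60/0.90 = 0.67 | 0.30 | 0.60/0.30 = 2.00 |

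**The case against.** The strongest defence is that the sentence begins with *For instance* and does not define *integrate*. It does not say that EMA replaces the PAS in one arm. EMA–PAS agreement in the intervention arm could, for example, inform a range of recall error applied to both arms, and a condensed article may leave such detail to a fuller plan. This stands in part: one-arm substitution is a possible reading, not a stated method, so the table shows a conditional risk. What does not stand is the idea that a later plan could supply the missing input. It cannot create control-arm EMA data. Applying a recall-error range learned in one arm to both would assume that recall works alike in people who keep a daily diary and people who do not.

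The Intervention section also offers participants help with installing the app throughout the study. That sentence describes support for the training, which controls do not have before t3.

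Three stronger readings are tempting, and the documents do not support them:
- **That the analysis would flatter the intervention.** A reader might take this from the Background, which says of electronic diaries "which are likely biased by memory effects because clients must complete these diaries retrospectively". That passage concerns diaries kept on desktop PCs or laptops, not the PAS, and gives no direction. Recall could overstate or understate severity.
- **That diary entries are known to stop after week 5.** Table 1 lists content and homework by week, and the Diary data section gives no end date. Only the absence of scheduled EMA collection at T1 to T3 can be stated.
- **That the economic evaluation as a whole is compromised.** The base case uses the PAS, and quality of life is measured with the EQ-5D and SF-12. All three are collected in both arms at T0 to T3.

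**Conclusion.** The point holds. As written, the analysis cannot do what it is meant to do, because the data intended to correct the between-arm effect exist in one arm only, measure something other than the PAS, and are not scheduled at the post-baseline assessments. This conclusion rests on reading the app as the only EMA source and as unavailable to controls before t3, which every relevant section supports.

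Whether the result would be biased, and by how much, depends on how EMA is used. If it adjusts one arm only, the bias equals the method difference and may go either way. The 0.1 to 0.3 SD range is an assumption, and d = 0.60 is the planning value, not an estimate for the six-month economic horizon.

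Severity is minor to moderate: one illustrative sensitivity analysis is affected. The base-case cost-effectiveness and cost-utility analyses and the primary PAS analysis do not use EMA.

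**What to change.** In Economic analyses, remove EMA from the sensitivity analysis of the between-arm result and state that this analysis uses only inputs measured in both arms. Report EMA separately and descriptively within the intervention arm, for example as its agreement with the PAS.

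This changes one sentence and affects no participants or data collection. The small price is that the trial gives up the claim of correcting recall bias in the ICER, a claim the design cannot support.
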